### Confidentiality {27}

To ensure participant confidentiality, on referral to the study participants from each site involved will be allocated a unique identification (ID) number which will be used for all subsequent data collection, and hard copy and electronic copy stored as per local privacy standards. Any personal information collected from participants will be de-identified using ID numbers and re-identifiable if needed using the master list only. All stored data will be destroyed after 15 years of study completion in accordance with current Health Research Ethics Committee (HREC) requirements, using deletion and shredding protocols.

### Plans for collection, laboratory evaluation, and storage of biological specimens for genetic or molecular analysis in this trial/future use {33}

Not applicable to this study, no samples collected.

## Statistical methods

### Statistical methods for primary and secondary outcomes {20a}

Participant demographic, clinical characteristics, and study outcomes will be presented using standard descriptive statistics, including mean, standard deviation and range or median, quartiles and range for continuous variables, frequencies and percentages for categorical variables, and the Kaplan–Meier method for time to event variables. All statistical analyses will use the intention to treat principle whereby participants are analyzed in their randomized groups, regardless of treatment received. The primary outcome of the number of responses in each treatment arm will be compared using a chi-square test and the difference in proportions presented with a 95% confidence interval. Other study outcomes will be compared between randomized groups using standard tests, including chi-square tests for categorical outcomes, two-sample *t*-tests or nonparametric equivalent for continuous outcomes, Poisson regression models for count data, and log-rank test for time-to-event data. For longitudinal outcomes, statistical models that account for the correlation between repeated observations in the same participant will be used. A more detailed pre-specified statistical analysis plan is forthcoming with completion of the trial and will be made publicly available.

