### Objectives and hypothesis {7}

#### Primary research question

Does a modified adult chronic condition self-management program plus standard care improve therapy adherence in adolescents aged 15–18 years with a chronic condition compared to standard care only?

The *primary objective of this stud*y is to investigate the effectiveness via adherence of a modified adult chronic condition self-management support program in an adolescent population with a chronic condition within a tertiary pediatric hospital setting, compared to those receiving routine care services in the same setting using standardized markers of improvement in control of their chronic illness.

The *secondary objectives* include the use of routinely collected data on the number of unplanned or unscheduled health care or emergency department visits, together with questionnaire measures of quality of life, self-efficacy, time management, health-related distress, and feasibility and acceptability of the program to further refine its delivery under clinical conditions.

*Study hypothesis* to be tested is that a modified adult-focused, generic chronic condition self-management support program provided to adolescents with a chronic condition who are in the active phase of transition to adult services would:Be more effective than standard usual care in achieving adherence to chronic condition management as measured by quantitative condition-specific validated markers of improvement in illness control as described in Table 1.Be more effective than standard care in improving more global quality of life, self-efficacy, time management, and in reducing health-related distress as described in Table 2.

**Table 1 Tab1:** Markers of illness control

Chronic condition	Measures of illness control	Definition of improvement^*^
Cystic fibrosis	▪ FEV1	FEV1% of predicted increased by ≥ 10%
Type 1 diabetes mellitus	▪ HbA1c	Absolute decrease in HbA1C by ≥ 1% (e.g., 9% reducing to 8%)
Inflammatory bowel disease	▪ Weight	Absolute increase in weight by ≥ 5%
Chronic kidney disease	▪ GFR	Absolute increase in GFR by ≥ 5%
Asthma	▪ FEV1	FEV1 % of predicted increased by ≥ 10%
Epilepsy	▪ Number of seizures	Based on individual and type of seizure as negotiated with treating Neurologist.

Abbreviations measures of illness control: *FEV1 (%)* forced expiratory volume in 1 s, *HbA1c* glycosylated hemoglobin (mmol/mol), *GFR* glomerular filtration rate (mL/min)

Weight (kilograms)

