### Trial design {8}

This is a pragmatic, two-site, two-arm, parallel, longitudinal randomized controlled trial, using both quantitative and qualitative research methods. Participants are allocated at a ratio 1:1 to the intervention or usual care using a computer-generated random list. An RCT design was chosen for this study due to its accepted applicability in assessing the effects of new healthcare interventions such as a self-management program [37, 38]. This study design has been shown to demonstrate sound methodological evidence [39], and allows for a comparison group at each time period and for analysis between each cluster [37, 40]. The study protocol received approval by The Sydney Children’s Hospitals Network Human Research Ethics Committee, Sydney, Australia. The study protocol has been developed based on the Standard Protocol Items: Recommendations for Interventional Trials (SPIRIT) guidelines Schulz and Grimes [41] (see Additional File 1). Figure 2 demonstrates the flowchart of the study design.

This protocol describes an RCT to demonstrate the efficacy of the Flinders Program™ in adolescents. Following randomization, participants in the intervention group will receive a 12-month nurse-led modified version of the Flinders Program™ plus standard care, while participants in the waitlist control group will receive standard care for 6 months before crossing over to the intervention group until all participants are exposed to the program as demonstrated in the study design diagram in Fig. 1. Given that the data available suggests continuing deterioration without intervention is expected, we consider it ethically responsible to offer the intervention to both participant groups.

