### Sample size {14}

The primary outcome of a response to treatment is defined by improvement in disease markers listed in Table 1. We estimate that fewer than 15% of participants would show improvement in disease under usual care, and the intervention would only be considered worthwhile implementing if it can improve responses by a substantial margin. A study conducted by Rhee and colleagues, which evaluated the effectiveness of a self-management program for adolescents with asthma, found overall the intervention group reporting greater improvements in outcome measures; knowledge, self-management skills self-efficacy, and Quality of Life (QOL), than the control group [66]. A study of 54 participants (27 per group) will have 80% power at 5% two-sided alpha to detect a difference in response rates between treatment arms if the rate under usual care is 15% or less and the true difference in proportions is at least 35%, using a chi-square test. To allow for some loss to follow-up, we plan to recruit a total of 60 participants. Participants who withdraw from the study will not be replaced as the power analysis allows for attrition. Participants who withdraw from the study, may have their clinical outcomes determined from their medical records to ensure that the results of the research study can be measured accurately.

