## Assignment of interventions: allocation

### Sequence generation {16a}

Following formal consent, the participants will be randomized. Successively, baseline data collection and measures of illness control will be collected for both the control and intervention groups. Randomization will be stratified by disease condition (diabetes, CF, renal, inflammatory bowel disease, other) and will use permuted blocks to maintain balance.

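### The primary chi-square test leaves out the five disease strata used in randomization; it stays valid and adequately powered, but gives up some precision if response rates differ clearly between conditions

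*Protocol article*

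**What the plan says.** All references are to the protocol article.

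- Sequence generation {16a}: "Randomization will be stratified by disease condition (diabetes, CF, renal, inflammatory bowel disease, other) and will use permuted blocks to maintain balance".
- Statistical methods for primary and secondary outcomes {20a} fixes the test: "The primary outcome of the number of responses in each treatment arm will be compared using a chi-square test". The effect measure that goes with it, in the same section, is "the difference in proportions presented with a 95% confidence interval". The strata are not mentioned.
- Sample size {14}: "A study of 54 participants (27 per group) will have 80% power at 5% two-sided alpha". The condition attached to this figure is "if the rate under usual care is 15% or less and the true difference in proportions is at least 35%, using a chi-square test". On recruitment: "To allow for some loss to follow-up, we plan to recruit a total of 60 participants".
- Trial design {8}: "Participants are allocated at a ratio 1:1 to the intervention or usual care".
- Table 1 (under Objectives and hypothesis {7}) defines response by condition: FEV1 for cystic fibrosis and asthma, HbA1c for diabetes, weight for inflammatory bowel disease and GFR for chronic kidney disease, each with its own threshold. For epilepsy the entry reads "Based on individual and type of seizure as negotiated with treating Neurologist". Under Measures of illness control, conditions outside the table get a definition agreed with the referring team.

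No section gives expected response rates or participant numbers by condition. Section {20a} announces a more detailed analysis plan, but has already named the primary test and effect measure.

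**The concern.** The strata in the randomization have no counterpart in the primary analysis. Stratified blocking keeps the arms alike in disease mix, so differences between conditions contribute little to the real sampling variation of the treatment difference. The crude binomial variance still counts those differences. If response rates differ between conditions, the crude standard error is too large, the test rejects too rarely under the null, and power is lost.

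Unequal rates are plausible here, because meeting a threshold in HbA1c, lung function, weight or GFR is a different event in each group. With 54 evaluable participants there is little precision to spare.

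**Working it through.** **1. The plan's own figure.** Inputs from Sample size {14}: p1 = 0.15, p2 = 0.50, two-sided 5%, 80% power. Chi-square formula without continuity correction, with mean rate 0.325:

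n = [1.960·√(2·0.325·0.675) + 0.842·√(0.15·0.85 + 0.50·0.50)]² / 0.35² = 26.9, so 27 per group.

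Power at 27 per group is 80.2% by this approximation and 82.0% by exact enumeration of the uncorrected Pearson test. The stated 54 reproduces. With a continuity correction it would be 33 per group, so the plan evidently used the uncorrected test, as do the steps below.

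**2. Why the crude variance is too large.** Let w_k be the share of stratum k and p_k its response rate in one arm, with overall rate p. Then

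p(1−p) = Σ w_k p_k(1−p_k) + Σ w_k (p_k − p)².

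The crude variance uses the left side. With balanced strata only the first term on the right is real sampling variation.

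Example, strong spread (assumed): strata of 12/12/10/10/10, control rates 2/2/5/30/40%, intervention rates 20/25/50/75/85%. The overall rates are 14.8% and 48.9%.

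- Crude: 0.148·0.852 + 0.489·0.511 = 0.376; SE = √(0.376/27) = 0.118.
- Between-stratum terms: 0.025 (control) + 0.068 (intervention) = 0.093.
- Within strata: 0.376 − 0.093 = 0.283; SE = √(0.283/27) = 0.102.

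The ratio is 1.15. This is the limit under perfect balance. Incomplete blocks leave some imbalance, and the average estimated SE lies slightly below its formula value, so simulation gives a smaller ratio.

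**3. Simulation near the planned effect.** 200,000 trials per scenario, 54 evaluable, 1:1. Stratum sizes (as above), block size 4 and the rates by condition are assumptions. Overall rates stay at 14-15% vs 49-50%.

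| Spread (control; intervention rates) | Power, chi-square | Power, CMH | Mean crude SE | True SD | Type I error, chi-square | Type I error, CMH |
|---|---|---|---|---|---|---|
| Equal (15%; 50%) | 81.5% | 80.6% | 0.1158 | 0.1180 | 5.1-5.2% | 4.9-5.0% |
| Mild (5-25%; 40-60%) | 82.3% | 82.3% | 0.1153 | 0.1161 | 4.7-5.0% | 4.8-5.0% |
| Moderate (5-30%; 30-70%) | 82.0% | 83.9% | 0.1152 | 0.1121 | 4.1-4.4% | 4.7-5.0% |
| Strong (2-40%; 20-85%) | 82.7% | 89.0% | 0.1161 | 0.1037 | 3.1-3.2% | 4.8-5.0% |

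Crude SE over true SD: 0.1152/0.1121 = 1.03 (moderate) and 0.1161/0.1037 = 1.12 (strong). CMH minus chi-square power: −0.9, 0.0, +1.9 and +6.3 points.

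With 60 evaluable and unequal strata (18/8/8/10/16), the power differences are −0.3, +0.8, +2.8 and +7.2 points.

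**4. Interval coverage at 54.** The crude interval covers 93.9% (equal), 94.2% (mild), 95.0% (moderate) and 96.6% (strong). The Mantel-Haenszel interval (Sato variance) covers 93.8%, 93.7%, 93.9% and 94.5%. So the stratified interval is narrower when conditions differ, but at this size it runs slightly under its nominal level.

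**The case against.** The planned analysis is coherent: the trial is sized on a chi-square test and analysed with one. Leaving out the strata brings no bias and does not inflate type I error. The quantity that decides the size of the loss, the spread of response rates across conditions, is not in the document. Different thresholds make unequal rates plausible but do not show that they are far apart, and a mild spread costs nothing. All of this stands, and it limits the weight of the point.

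The deferral to a later analysis plan carries less force. Adjustment for strata is often settled there, but this article has already named the primary test and effect measure, and a different choice would have to replace them.

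A reader might infer that ignoring the strata leaves the trial badly underpowered. Scenarios that apply one odds ratio of 5.67 (15% vs 50%) to widely differing control rates seem to show this, but they shrink the overall effect. With strata of 16/8/8/12/10, control rates of 5/5/35/30/10% give 15.9% vs 44.3% overall, and 5/5/50/50/5% give 21.7% vs 46.0%. These are differences of 28 and 24 points, against the planned 35. Most of the fall in power there comes from the smaller effect, so such scenarios do not measure the cost of leaving out the strata.

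**Conclusion.** The mismatch between stratified randomization and unstratified primary analysis is real and worth correcting, as a point of efficiency and calibration. At overall rates near 15% vs 50% and 54 evaluable participants, the plain chi-square keeps 81.5-82.7% power in every scenario run, so the sample size is not in question.

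Under an assumed moderate to strong spread, the crude standard error is about 3% to 12% too wide, type I error drops to about 3-4%, and about 2 to 6 points of power are given up. Under a mild spread there is neither loss nor conservatism; with equal rates the stratified test is about 1 point worse. These figures rest on assumed rates by condition, stratum sizes and block size. The direction follows from the design; the amount cannot be fixed from the document. It would go too far to call the error bars too wide whenever response differs by condition, or to call the planned test invalid.

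**What to change.** In section {20a}, name as primary test a Cochran-Mantel-Haenszel test (without continuity correction, as in the sizing) stratified by the five randomization groups. Report the Mantel-Haenszel risk difference with its 95% confidence interval, state the variance estimator, and keep the unstratified chi-square and crude difference as a sensitivity analysis. Carry the same wording into the forthcoming analysis plan, and settle it before outcomes are compared by arm. If the relative risk promised under Measures of illness control is also reported, use the same strata for it.

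The cost is one sentence of wording. Disease group is already recorded for randomization, and the sample size need not change. The price is about 1 point of power if conditions do not differ, and interval coverage slightly below 95% at this sample size. Stratifying also cannot remove differences within the residual group, which pools asthma, epilepsy and any condition not listed.

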### Interim analyses {21b}

There is no planned interim analysis for this trial.

### Methods for additional analyses (e.g., subgroup analyses) {20b}

Not applicable to this study. No additional subgroup analyses have been planned.

### Methods in analysis to handle protocol non-adherence and any statistical methods to handle missing data {20c}

The primary aim of this study is to evaluate the effectiveness of a modified adolescent-friendly version of an adult self-management program within a clinical environment. To allow for some loss to follow-up, we plan to recruit a total of 60 participants. All available data will be analyzed on an intention-to-treat basis, whereby participants are analyzed according to their randomized treatment allocation group, regardless of whether they actually received the intervention, their subsequent withdrawal or deviation from the intervention. There is no intention to impute missing data.

Participants can withdraw from the study at any time. If the patient decides to withdraw from the study, data collected will be retained as outlined in the consent and the reasons for the withdrawal will be recorded for subsequent analysis in the interpretation of results. Participants who withdraw from the study will not be replaced unless attrition is higher than anticipated as we require 30 participants in each group. Participants who withdraw from the study may have their clinical outcomes determined from their medical records to ensure that the results of the research study can be measured accurately.

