#### Follow-up data collection

Adherence to prescribed treatment regimenBaseline observations will be collected from both the waitlist control group and the intervention group before randomization. Potential participants in the intervention group will be contacted via phone by a member of the research team. Follow-up of participants in the intervention group will be undertaken by a member of the research team via phone or telehealth (depending on the young person’s preference) at 3, 6, and 12 months to follow-up on adherence to the prescribed treatment post intervention. Participants who do not respond to 3 attempts to contact them at any time point will be treated as missing data.

Information from the participants will be obtained by completing the PIH scale via a semi-structured interview. Subsequently, participants allocated to the wait list control group will be contacted by phone by a member of the research team and provided with a self-management information brochure, with no further contact from the research team. At 6 months, participants in the waitlist control group will be contacted by phone by a member of the research team and invited to participate in the intervention as described for the initial intervention group.(b)Markers of illness control and unplanned hospital visits

The research team will obtain standard measures of illness control for all participants who have been recruited into the study and who have consented to clinical information being obtained for research purposes. The control of chronic illness is the best quantitative measure of therapy adherence that is available. This will be undertaken by way of the research team extracting information from the electronic medical records (EMR) and the young person’s primary physician contacted for further information. Data on unplanned hospital visits will be retrieved by the research team from EMR and/or accessed through the young person’s My Health Record if available.

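### The primary responder analysis is fixed as available-case under an intention-to-treat label, with record retrieval after withdrawal only optional, so a few losses concentrated in one arm could overstate the difference or decide significance

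*Protocol article*

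**What the plan says.** **Analysis set and missing data.** Section {20c} of the protocol article states "All available data will be analyzed on an intention-to-treat basis", by allocated group whatever treatment was received, and then "There is no intention to impute missing data".

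**Primary test.** Section {20a}: "The primary outcome of the number of responses in each treatment arm will be compared using a chi-square test", with the difference in proportions and its 95% confidence interval. The outcome is yes/no: sustained improvement over 12 months in a condition-specific marker (Table 1 and Measures of illness control).

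**Size.** Section {14}: "A study of 54 participants (27 per group) will have 80% power at 5% two-sided alpha", "if the rate under usual care is 15% or less and the true difference in proportions is at least 35%, using a chi-square test". It continues: "To allow for some loss to follow-up, we plan to recruit a total of 60 participants". Section {8}: "Participants are allocated at a ratio 1:1 to the intervention or usual care".

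**Source of the outcome.** Follow-up data collection, part (b), takes the marker from the electronic medical record (EMR) for all recruited participants who consented to this, with the primary physician contacted for further information. For participants who withdraw, sections {14} and {20c} both use the permissive *may* for determining outcomes from records.

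**Non-contact.** Part (a) of Follow-up data collection, on phone and telehealth follow-up, says: "Participants who do not respond to 3 attempts to contact them at any time point will be treated as missing data". It does not say whether this reaches the EMR marker.

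**The concern.** The article states a rule here; it does not merely leave a gap for the statistical analysis plan (SAP). With available data only and nothing imputed, a chi-square test on responders uses as its denominator the participants whose outcome is known. Intention-to-treat then describes only how participants are grouped. It does not mean that everyone randomised is counted.

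The article gives reasons to expect some loss, and for that loss to relate to outcome:

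- Section {8} cites the difficulty of retaining adolescents in research.
- Follow-up data collection treats illness control as the best available measure of adherence, so disengagement could plausibly go with not improving.
- The Discussion places transfer to adult care typically at 17–18 years, inside the 15–18 eligibility range. Some participants may leave the network's records during follow-up.

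If non-improvers drop out of one denominator more than the other, that arm's response rate is inflated. In a trial of 60, this can change both the reported difference and the p-value.

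**Working it through.** **1. The plan's own figure.** Inputs from {14}: control 15%, difference 35 points (so intervention 50%), two-sided alpha 5%, power 80%. The mean rate p̄ is 0.325.

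n per arm = [1.960·√(2·0.325·0.675) + 0.842·√(0.15·0.85 + 0.50·0.50)]² / 0.35² = (1.298 + 0.517)² / 0.1225 = 26.9, so 27.

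Power at 27 per arm is 0.80, so the stated figure reproduces. The implied loss is (60 − 54)/60 = 10%; no percentage is stated.

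**2. Test used below.** Uncorrected Pearson chi-square: χ² = (p_I − p_C)² / [p̄(1 − p̄)(1/n_I + 1/n_C)].

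Example with all six losses in the intervention arm:

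- Available case, 4/30 v 10/24: p̄ = 14/54; χ² = 0.2833² / (0.1920 × 0.0750) = 5.57; p = 0.018.
- All randomised, missing as not improved, 4/30 v 10/30: p̄ = 14/60; χ² = 0.2000² / (0.1789 × 0.0667) = 3.35; p = 0.067.

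**3. Scenarios.** Six of 60 missing. The split and the responder counts are assumptions.

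| Losses (control + intervention) | Available case | p | All 60, missing as not improved | p |
|---|---|---|---|---|
| 3 + 3 | 4/27 v 13/27 (33 points) | 0.008 | 4/30 v 13/30 (30 points) | 0.010 |
| 1 + 5 | 4/29 v 11/25 (30 points) | 0.013 | 4/30 v 11/30 (23 points) | 0.037 |
| 0 + 6 | 4/30 v 12/24 (37 points) | 0.003 | 4/30 v 12/30 (27 points) | 0.020 |
| 0 + 6 | 4/30 v 10/24 (28 points) | 0.018 | 4/30 v 10/30 (20 points) | 0.067 |

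**4. Bounds for 3 + 3 loss with 4/27 v 13/27 observed** (no missing intervention participant improved):

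- Two of three missing controls improved: 6/30 v 13/30, p = 0.052.
- All three improved: 7/30 v 13/30, p = 0.100. The difference is still 20 points in favour of the intervention.

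**5. How often significance would be lost.** Participants with a known outcome respond at 15% and 50%, and the available-case result is significant in favour of the intervention. Binomial enumeration gives the share of such results that lose significance:

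- 3 + 3 loss, missing as not improved: 2.9%.
- 0 + 6 loss, missing as not improved: 28%.
- 3 + 3 loss, full worst case: 51%.

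**6. False positives.** Take a true rate of 15% in both arms of 30, with six non-improvers lost from the intervention arm only. The available-case test rejects in 7.4% of trials, against 5.3% when all 60 are counted.

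**The case against.** The strongest reply is that little will be missing. The marker comes from the EMR, not from contact with the participant, and outcomes after withdrawal can be looked up. The three-attempts sentence belongs to the phone and telehealth part of follow-up, so an unanswered call does not by itself make the marker missing. This stands, and it limits the likely number of missing outcomes. It does not remove the problem, because retrieval after withdrawal is optional and the reach of the three-attempts rule is not stated.

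The loss pattern is also uncertain. No data in the article link missing markers to poor control. The extra calls to the intervention arm are presented as retention measures ({11c}, {18b}) and could reduce loss there.

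Counting missing as not improved is itself a single imputation. Transfer to adult care is administrative and is not evidence of failure. If losses were heavier among controls, the rule would flatter the intervention. This is why it is proposed beside bounds and the available-case result, and not as the only answer.

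A reader might infer three stronger points, which the document does not support:

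- *That the conclusion could reverse.* In the cases checked, significance is lost but the sign does not change. The full worst case needs every missing control to have improved, which sits badly with an assumed usual-care rate of 15% or less.
- *That no sensitivity analysis is planned.* The article is silent, and {20a} announces a more detailed SAP that is not shown.
- *That 10% loss is a stated assumption.* It is only implied by going from 54 to 60.

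**Conclusion.** The point holds in a limited form. The article fixes an available-case primary analysis, labels it intention-to-treat, and leaves record retrieval after withdrawal optional.

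With six losses split evenly and counted as not improved, the result barely moves. With losses concentrated in the intervention arm, the difference is overstated by about 7 to 10 points in the scenarios above, and a result of moderate strength can lose significance. A result at the full design effect (12/24 observed) keeps it. These sizes rest on the implied 10% loss, an assumed split between arms and assumed outcomes for the missing. If retrieval is nearly complete, the effect will be smaller.

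The SAP may add sensitivity analyses, but it could not replace the stated no-imputation rule without departing from {20c}. The remedy is cheap enough to make the change worthwhile.

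**What to change.** 1. In {14} and {20c}, change *may have* to *will have, where consent allows*. The endpoint marker is then sought from the EMR or the treating physician for every randomised participant.
2. In Follow-up data collection, state that the three-attempts rule applies to contact-based data and not to the EMR marker.
3. In {20c}, replace the blanket no-imputation sentence with an analysis of all 60 randomised participants that counts missing as not improved, plus best/worst-case or tipping-point bounds. Report these beside the available-case result.
4. Describe the available-case result as available-case by randomised arm.

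Cost: two extra tabulations, some record-retrieval work, and possibly slightly less favourable response rates.
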